#### **14.2.5 Intracellular drug concentration**

Assuming Week 16 intracellular drug concentration has a log-normal distribution with a between subject standard deviation of 1.0 on the natural logarithm scale, this study should have about 79% power to rule-out a two-fold or greater relative decrease in the geometric mean concentration due to intermittent versus daily FTC/TDF. If the between subject standard deviation is 0.5, then there will be about 80% power to rule-out a 1.5-fold or greater decrease in the geometric mean concentration.

Pharmacokinetic (PK) modelling using plasma and intracellular drug concentrations will be performed to estimate individual PK parameters based on 2 drug levels following an observed dose, body weight, and creatinine clearance, and informed by population-PK parameter estimates. The MEMS data will be combined with the individual PK

estimates to simulate concentration-time relationships for the study. The PK-MEMS simulated concentrations will be compared to observed concentrations to evaluate plausibility of the reported dosing behaviour in comparison to that which is observed. Individual estimates of mean trough concentrations (plasma and intracellular) will be estimated. Comparisons between intermittent and daily regimen will be compared using actual and simulation-based values.

Intracellular drug levels will be correlated with pill count and self report data for those volunteers reporting drug use in the past 48 hours. Levels of drug in hair samples will be evaluated for exploratory purposes only.

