|                                                   | 
Daily dosing: 1 tablet orally per day
 
Intermittent dosing: 1 tablet orally Monday and Friday and again within 2 hours after sexual intercourse (except on Monday or Friday), not to exceed 1 dose per day.
 
PO = Oral
                                                                                                                                                                                                                                                                                                                                                                                                                                                                                                                                                                                                                                                                                                                                                                                        |
| METHODS:                                   | See Schedule of Procedures; Appendix A1 and A2                                                                                                                                                                                                                                                                                                                                                                                                                                                                                                                                                                                                                                                                                                                                                                                                                                                                                                                                                                                   |

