Because deployment of IVR or SMS to collect data in Uganda is a new procedure and not without risk of technical, logistical, or cultural obstacles, this pilot study will assess feasibility and participant burden. Feasibility will be assessed by percentage of study days with missing data and participant burden will be assessed by 5 point Likert scale. It will also determine if IVR is more sensitive at detecting sexual behavior than a 30-day timeline follow-back procedure. In the event that IVR is not practical, the 30-day timeline follow-back interviewing can be used as the primary sexual behavior measure [141, 142].

*Impact of daily measurements on sexual behaviour.* Daily measurements may change sexual behaviour. In a recent study of IVR in 44 Hispanic students, there was a modest temporary decrease in sexual behavior self-reports over time from an average of 0.375 sexual episodes per day

during the first three weeks of IVR reporting to 0.25 episodes per day over 9 weeks an increase towards baseline at the end of the 13-week period [140]. Similar temporary reductions have been reported with IVR measurement of alcohol consumption. Helzer, for example, reported an average decline in alcohol consumption of about 19% over a two year period in a study of daily self-reporting using IVR [137]. In sum, daily self-reports bear the risk of reactivity either in form of socially desirable responding or as a true effect on behaviour. However, these changes may be temporary, and the increase in measurement precision in knowing the extent to which PrEP adherence is associated with sexual behaviour likely outweighs the potential impact on behaviour.

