##### *Intracellular drug concentrations:*

- The mean intracellular drug concentration for each group assigned to FTC/TDF

*Adherence:*

- The proportion of volunteers, who by MEMS data, took at least 80% of expected doses of the investigational product
- The proportion of volunteers assigned to FTC/TDF who have detectable drug plasma levels within 48 hours of reported use
- The relationship between intracellular drug levels and adherence in volunteers assigned to FTC/TDF

*Behavioural:*

- Reported number of steady and casual sex partners
- Frequency of unprotected vaginal intercourse
- Substance use prior to or during sex

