## **14.0 STATISTICAL CONSIDERATIONS**

### **14.1 Sample Size**

Approximately 72 volunteers (24 daily FTC/TDF, 24 intermittent FTC/TDF, and 24 combined placebo recipients) who meet all eligibility criteria will be enrolled in the study.

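### The two stated drug-level powers, about 79% and about 80%, cannot both hold at one significance level when no true difference is assumed, and the protocol states neither the level nor the assumed ratio

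*Protocol*

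**What the plan says.** Section 5.1.1 lists among the primary endpoints "The mean intracellular drug concentration for each group assigned to FTC/TDF". Section 14.1 sets the arm sizes: "Approximately 72 volunteers (24 daily FTC/TDF, 24 intermittent FTC/TDF, and 24 combined placebo recipients".

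Section 14.2.5 plans the comparison of intermittent with daily FTC/TDF at Week 16. It takes log-normal concentrations with a "between subject standard deviation of 1.0 on the natural logarithm scale" and states that "this study should have about 79% power to rule-out a two-fold or greater relative decrease in the geometric mean concentration". For an SD of 0.5 it adds that "there will be about 80% power to rule-out a 1.5-fold or greater decrease in the geometric mean concentration". The Synopsis (Statistical Considerations) gives the same two figures.

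Neither place gives a significance level, a sidedness or a true ratio. Nearby sections are more explicit. The adherence power (14.2.4) and the condom-use power (14.2.6) both use a two-sided 0.05 test. The safety intervals (14.2.1) are two-sided 95%, and the rule-out power for adverse events in 14.2.1 says that it assumes no real increase.

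The intermittent regimen in the Synopsis is "1 tablet orally Monday and Friday and again within 2 hours after sexual intercourse", apart from sex on the two fixed days, with at most one dose a day. That allows 2 to 7 doses a week, against 7 for daily dosing.

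**The concern.** The two scenarios are not equally hard. Halving the SD helps more than shrinking the margin from two-fold to 1.5-fold hurts, so under no true difference the second case must have clearly higher power than the first at any common alpha. Printing them one point apart suggests that they were computed at different levels.

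The comparison matters to the pilot. Section 3.7 makes intracellular levels similar to those of daily PrEP one of the findings that would support a larger phase 2 study. If the two-sided 0.05 convention applies, the chance of failing to exclude a two-fold fall when there is none is 33%, not the 21% that a reader would take from the text.

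**Working it through.** **Inputs.** 24 per arm (Section 14.1). SD 1.0 with margin ln 2 = 0.693, and SD 0.5 with margin ln 1.5 = 0.405 (Section 14.2.5). A true ratio of 1 is my inference, by analogy with the adverse-event calculation in 14.2.1.

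**Formula.** SE = SD × √(2/24). Power = Φ(margin/SE − z), where z is the one-sided critical value.

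- Two-fold, SD 1.0: SE = 0.2887, margin/SE = 2.401.
- 1.5-fold, SD 0.5: SE = 0.1443, margin/SE = 2.809.

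**Reproducing the printed figures.**

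| One-sided alpha | Two-fold, SD 1.0 | 1.5-fold, SD 0.5 |
|---|---|---|
| 0.025 (z = 1.960) | Φ(0.441) = 67.0% (t: 65%) | Φ(0.849) = 80.2% (t: 79%) |
| 0.05 (z = 1.645) | Φ(0.756) = 77.5% (t: 76%) | Φ(1.164) = 87.8% (t: 87%) |
| Printed | about 79% | about 80% |

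Each figure is matched alone: the 79% approximately at one-sided 0.05, the 80% at one-sided 0.025. Solving backwards, 79% needs z = 2.401 − 0.806 = 1.595, a one-sided alpha of 0.055. The 80% needs z = 2.809 − 0.842 = 1.967, an alpha of 0.025.

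**Rounding does not explain it.** At 24 per arm the two cases differ by 2.809 − 2.401 = 0.41 on the z scale whatever alpha is used. Powers of 79% and 80% differ by 0.842 − 0.806 = 0.035. A search over 12 to 40 per arm and one-sided alpha from 0.001 to 0.25, by normal and t calculations with a true ratio of 1, found no setting within 2 points of both figures. Dropout or the permitted 10% over-enrolment therefore does not rescue the pair.

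**Sensitivity to the true ratio.** With ratio r, power = Φ((margin + ln r)/SE − z). If exposure is proportional to doses taken and adherence is equal in both arms, r = doses per week / 7. For 5 doses, ln(5/7) = −0.336. The two-fold case is (0.693 − 0.336)/0.2887 = 1.236 before subtracting z. The 1.5-fold case, computed without intermediate rounding, is 0.478.

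| Doses/week | Ratio | Two-fold, SD 1.0 (0.025 / 0.05) | 1.5-fold, SD 0.5 (0.025 / 0.05) |
|---|---|---|---|
| 7 | 1.00 | 67% / 78% | 80% / 88% |
| 6 | 0.86 | 46% / 59% | 41% / 54% |
| 5 | 0.71 | 23% / 34% | 7% / 12% |
| 4 | 0.57 | 7% / 12% | under 1% |

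The column labels 0.025 and 0.05 are one-sided levels.

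**The case against.** **Which figure is wrong is not settled.** Section 14.2.5 describes a one-directional rule-out and names no alpha. At one-sided 0.05 the 79% is nearly right (77.5%) and the 80% is the faulty figure, too low against 88%. This objection stands. A reader might infer that the chance of excluding a two-fold fall is simply overstated, but that follows only if the neighbouring two-sided 0.05 level applies here too.

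**Other readings might reconcile the pair.** Treating 1.0 and 0.5 as coefficients of variation gives 81% and 83% (t, two-sided 0.05, 24 per arm). The text, however, defines them as SDs on the natural logarithm scale. A true ratio of 0.9 also brings the two powers together: (0.693 − 0.105)/0.2887 = 2.036 and (0.405 − 0.105)/0.1443, which is 2.079 without intermediate rounding. Subtracting 0.806 and 0.842 leaves z of about 1.23 and 1.24, a one-sided alpha of about 0.11. The protocol states neither that ratio nor that level, so this shows only that the assumptions need to be written down.

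**Assuming no true difference is a usual convention.** Section 14.2.1 uses it openly, and whether levels are similar is what the pilot is meant to find out. That is fair: the assumption needs disclosure and is not itself an error.

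**A stronger reading goes further than the documents do.** A reader might infer that equal levels are implausible and that real power is only 1% to 10%. That comes from applying 0.25 to 0.375 sex days per day to the five unscheduled days, with full adherence. The source figure, "from an average of 0.375 sexual episodes per day", counts episodes in 44 students (Section 3.3.3.4), and the protocol gives no frequency for couples in Masaka. Adherence also moves the answer. With daily dosing at the 74% that Section 3.3.3.1 reports from an earlier trial, and full intermittent adherence at 0.375, doses are 5.18 against 3.875. That is a 1.34-fold difference, with power of 29% or 40% at one-sided 0.025 or 0.05. A single Week 16 sample also depends on the time since the last dose.

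**Nor does the protocol treat a low level as proof of poor adherence.** Sections 14.2.3 to 14.2.5 already tabulate days of use, relate levels to MEMS execution and compare regimens using MEMS-informed PK simulation. The endpoint's use of mean where 14.2.5 uses geometric mean is loose wording that an analysis plan can settle.

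**Conclusion.** The inconsistency is real on the protocol's own inputs: 24 per arm, the stated SDs and margins, and a true ratio of 1. The matching pair is 67% and 80% at one-sided 0.025, or 78% and 88% at one-sided 0.05. One printed figure is therefore off by about 12 points (79 − 67) or about 8 points (88 − 80), and the text does not show which. Consistency with 14.2.4 and 14.2.6 points to the 79%.

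The dependence on the true ratio is a matter of disclosure. The values at 4 to 6 doses a week rest on dose proportionality and equal adherence, neither of which the protocol states for this comparison. They show how quickly power falls below a ratio of 1; they do not forecast this trial's result.

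The consequence is limited. Section 14.1 does not derive the 72 volunteers from this calculation, and no decision rule uses the two-fold margin. It still misstates the planned precision of a primary endpoint and is cheap to correct.

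**What to change.** In Section 14.2.5 and the Synopsis:

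- State one alpha and its sidedness for the drug-level comparison.
- Replace the pair with the matching figures: about 67% and 80% if the two-sided 0.05 level is kept, or about 78% and 88% if one-sided 0.05 is chosen.
- Say that these figures assume no true difference in geometric means.
- Add power over a range of true ratios below 1, such as the rows above for 4 to 6 doses a week, labelled as resting on dose-proportional exposure and equal adherence.

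This is a wording change in two places. Sample size, dosing and data collection stay as they are. Under the two-sided 0.05 level the stated power becomes less favourable; under one-sided 0.05 the first figure barely moves and the second rises.

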#### **14.2.6 HIV risk behaviour change**

HIV risk behaviour will be measured at each visit by the number of steady and casual partners reported in the previous month, frequency of unprotected sex acts, and substance use prior to or during sex. Methods for repeated measurements, such as linear mixed effects models, will be applied to these data to assess both individual and group level changes in HIV risk behaviour. These models will incorporate time on and off study treatment.

Assuming condoms are used always or frequently by 60% of volunteers at baseline, this study has 85% power to detect a decrease in condom usage by treatment group (n=24) if volunteers reduce the rate to 30%. A decrease to a rate of 40% would be detected with 49% power. Power is based on a two-sided, 0.05 level test of a binomial proportion.

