**6.2 Randomization Visit for HIV-uninfected volunteers**

*Prior to the randomization, research centre personnel will:*

- Answer any questions about the study
- Review interim medical history (including concomitant medications)
- Review screening safety laboratory data.
- Review the Informed Consent Document with the volunteer.
- Perform a symptom directed physical examination including vital signs (pulse, respiratory rate, blood pressure and temperature), and any further examination indicated by history or observation.
- Conduct an HIV risk behaviour assessment
- Conduct HIV pre-test counselling.
- Collect blood and specimens for all tests as indicated in the Schedule of Procedures (Appendix A1).
- Perform a pregnancy test for all female volunteers and obtain results prior to randomization.
- Conduct HIV risk reduction counselling and family planning counselling (for women)
- Conduct HIV post-test counselling

*After the randomization, research centre personnel will:*

- Collect Adverse Events and Serious Adverse Events
- Distribute investigational product with MEMS TrackCap
- Conduct adherence counselling
- Distribute SIM card or cell phone, if needed, for IVR or SMS
- Conduct IVR or SMS instruction

The volunteer will be assigned to a treatment arm (FTC/TDF or placebo) in a blinded fashion according to the instructions specified in the Study Operations Manual.

The investigational product will be distributed as specified in section 8.4 Distribution of Product.

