### **7.6 Adherence Counselling**

Adherence counselling will be performed at time points according to the Schedule of Procedures (Appendix A1). At each follow-up visit, research centre personnel will assess volunteer adherence through a structured interview (follow back timeline) and pill count.

The structured interview will focus on self-reported adherence to the study medication, self-reported sexual activity, drug sharing, and challenges to adherence since the last visit (e.g., travel, illness, etc.). Research centre personnel will provide individualized adherence counselling at each follow-up visit, using the answers to the structured interview and pill count to guide the counselling messages.

Adherence counselling should include the following elements:

- Basic education about study medications such as mechanism of action, dose and dosing schedule, potential side effects, and storage
- Discussion of the volunteer's beliefs and attitudes about taking the investigational product
- Encouragement to talk to study personnel about medication questions or concerns
- Identifying and overcoming barriers to adherence, such as scheduling and organizational skills, reminder devices, social support, and disclosure.
- Discussion about reasons not to engage in pill-sharing and how to handle requests from friends and family to borrow doses

Complete information on procedures for adherence counselling is described in the Study Operations Manual.

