## APPENDIX A1: SCHEDULE OF PROCEDURES

|                                                                                                                                                                                                                                                      | Screen | Rando |     |     |       |            |        |       |           |       | Final visit | HIV f/u 1 | HIV f/u 2 |
|------------------------------------------------------------------------------------------------------------------------------------------------------------------------------------------------------------------------------------------------------|--------|-------|-----|-----|-------|------------|--------|-------|-----------|-------|-------------|-----------|-----------|
| Study Week                                                                                                                                                                                                                                           |        | 0     | W1  | W2  | W4    | W4+ 24 hrs | W8     | W12   | W16 or ET | W24   |             |           |           |
| Visit Windows (Days)                                                                                                                                                                                                                                 |        | -42   | ± 1 | ± 2 | -7/+2 |            | - 7/+2 | -7/+2 | - 7/+2    | -7/+7 |             |           |           |
| Investigational Product                                                                                                                                                                                                                              |        |       |     |     |       |            |        |       |           |       |             |           |           |
| FTC/TDF/Placebo provision                                                                                                                                                                                                                            |        | X     |     |     | X     |            | X      | X     |           |       |             |           |           |

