| Pre-/Post HIV-test counselling                                                                                                                                                                                                                       | X      | X     |     |     | X     |            | X      | X     | X         | X     | X**         | X**       |           |
| HIV risk reduction counselling / Family planning counselling                                                                                                                                                                                         | X      | X     |     |     | X     |            | X      | X     |           | X***  | X           | X         |           |
| Adherence counselling                                                                                                                                                                                                                                |        | X     | X   | X   | X     |            | X      | X     |           |       |             |           |           |
| Follow-back interview (adherence, sexual risk behaviour, medication sharing)                                                                                                                                                                         |        |       | X   | X   | X     |            | X      | X     | X         |       |             |           |           |
| Acceptability assessment (focus group/individual interview)                                                                                                                                                                                          |        |       |     |     |       |            |        |       | X*        |       |             |           |           |
| IVR or SMS behavioural assessment                                                                                                                                                                                                                    |        | Daily |     |     |       |            |        |       |           |       |             |           |           |

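### One-month recall of partner count at Weeks 1 and 2 reaches mostly or about half into pre-randomization time, blurring the on-drug contrast for a primary behavioural endpoint

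*Protocol*

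**What the plan says.** Section 14.2.6 (HIV risk behaviour change) sets the measurement rule: "HIV risk behaviour will be measured at each visit by the number of steady and casual partners reported in the previous month". It then adds "frequency of unprotected sex acts, and substance use prior to or during sex", with no recall period of their own. The data go into methods for repeated measurements such as linear mixed effects models, and "These models will incorporate time on and off study treatment".

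Section 5.1.1 lists the partner count among the primary endpoints, under the behavioural heading.

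In Appendix A1 the row beginning "Follow-back interview (adherence, sexual risk behaviour, medication sharing" is marked at Weeks 1, 2, 4, 8, 12 and 16. It is not marked at randomization or at Week 24. The baseline value comes from the randomization visit, where section 6.2 tells staff, before randomization, to "Conduct an HIV risk behaviour assessment".

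Two other places bear on the recall period. Section 3.3.3.4 refers to a "30-day timeline follow-back procedure". Section 7.6 says the structured interview deals with self-reported adherence, sexual activity, drug sharing and "challenges to adherence since the last visit".

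**The concern.** A one-month look-back suits visits four weeks apart. At Weeks 1 and 2 it is longer than the time since randomization, so both answers contain pre-drug behaviour yet sit in the data as post-randomization observations. Section 14.2.6 does not set these visits apart.

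Section 3.6 names increased risk-taking on study drug as a possible risk, and this endpoint is meant to detect it in groups of 24. Two of its six follow-up values are half or more pre-drug time. Study drug stops at Week 16 (section 6.7) and no interview is scheduled afterwards. Apart from volunteers who stop early, the off-drug information therefore lies before randomization, and the on/off contrast depends on the boundary that the look-back crosses.

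**Working it through.** **The plan's own figure.** The only figures in 14.2.6 are powers of 85% and 49% for condom use falling from 60% to 30% or 40% (n=24, two-sided 0.05 binomial test). The exact test rejects at X ≤ 9 or X ≥ 20 (actual size 0.035) and gives 84.7% and 48.9%. The stated figures are correct and do not depend on the recall window as written.

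**Inputs for the overlap.** Visits fall on days 7, 14, 28, 56, 84 and 112. Windows are ±1 day at Week 1, ±2 at Week 2 and −7/+2 at Week 4 (Appendix A1). The length of a month is assumed to be M = 30 days; 14.2.6 gives no number, so 28 to 31 is also shown.

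**Pre-randomization share** = max(0, M − visit day) / M.

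| Visit | M = 30 | M = 28 to 31 | M = 30, across visit window |
|---|---|---|---|
| Week 1 | 23/30 = 77% | 75–77% | 73–80% |
| Week 2 | 16/30 = 53% | 50–55% | 47–60% |
| Week 4 | 2/30 = 7% | 0–10% | 0–30% |
| Weeks 8, 12, 16 | 0% | 0% | 0% |

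**Days shared by two look-backs (M = 30).** The Week 1 look-back runs from day −23 to 7, Week 2 from −16 to 14, and Week 4 from −2 to 28. Shared days are:
- Weeks 1 and 2: 23 (77%)
- Weeks 2 and 4: 16 (53%)
- Weeks 1 and 4: 9 (30%)
- later neighbouring visits: 2 (7%)

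**Illustration of the effect.** Suppose behaviour changes by d at randomization and stays there, and the measure is proportional to days covered. The six visits then read 0.23d, 0.47d, 0.93d, d, d and d.
- All-visit average: (0.233 + 0.467 + 0.933 + 3)d / 6 = 0.77d.
- Without Weeks 1 and 2: (0.933 + 3)d / 4 = 0.98d.
- Least-squares slope on weeks 0, 1, 2, 4, 8, 12, 16: 0.0563d per week, against 0.0278d for the undistorted step. The ratio is 2.02.

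The average is pulled towards zero while the slope is about doubled, because a step has been turned into a ramp.

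**The case against.** Several stronger readings are tempting, and the protocol does not support them.

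- **That all risk behaviour is affected.** The month is attached only to partner count. Section 9.5 records sexual activity and condom use by day, on the calendar and by IVR or SMS, so for those measures pre- and post-randomization days can be separated.
- **That change is understated by 77%, 53% or, on average, 23%.** Those sizes need a measure proportional to days. A count of distinct partners is not, least of all for steady partners among enrolled couples. The 23% also needs an unweighted six-visit mean, which the plan never names as its estimate. A contrast of Week 8, 12 or 16 with baseline shows the change essentially in full.
- **That the distortion always hides change.** A linear slope is exaggerated.
- **That 7.6 flatly contradicts 14.2.6.** The phrase in 7.6 ends a list and may govern only its last item. If it does govern sexual activity, the interview would not reach before randomization. This is an ambiguity to settle.

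It is also fair to say that visit coding belongs to the SAP, which is not shown, and that the models are to carry on- and off-drug time. That does not dispose of the point. The recall period is fixed in the protocol and governs what is asked. A visit-level on/off term cannot split one count that straddles day 0, and a fractional exposure term would do so only for a measure that adds up over days. Nor do daily partner numbers on the calendar sum to distinct partners over an interval.

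**Conclusion.** The point holds for partner count at Weeks 1 and 2, and marginally at Week 4. With a 30-day month, those values cover 77%, 53% and 7% pre-randomization time (Week 4 up to 30% if held early), and the first two share 23 of 30 days. In a model over all visits they blur the before/after-drug contrast and make an abrupt change look gradual. The shares follow from the stated recall period and schedule, given the assumed month length. The 0.77d average and the doubled slope are illustrations that rest on an immediate, constant change in a proportional measure. The later visits are sound, so the endpoint is weakened in its early part rather than lost.

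**What to change.** In section 14.2.6:

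- Keep the constant one-month recall for partner count, but exclude Weeks 1 and 2 from the on-treatment partner-count model. Use baseline and Weeks 4, 8, 12 and 16, with Week 4 limited to post-randomization calendar days where possible. On the illustrative assumption above, dropping Weeks 1 and 2 alone recovers about 98% of an immediate change.
- Derive unprotected acts and substance use from post-randomization days of the calendar or the IVR/SMS data, where they are recorded by day.
- State one recall period for each measure and align it with section 7.6.

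Do not replace the month with distinct partners since the previous visit and an offset for days. A volunteer with one constant partner would then show 1/7 per day at Weeks 1 and 2, 1/14 at Week 4 and 1/28 at Week 8, a false fourfold fall.

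The cost is a wording change and two early observations per volunteer lost from the partner model. They can still be reported descriptively.
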